Citicoline in acute ischemic stroke undergoing revascularization therapy is a randomized controlled trial aiming to detect whether citicoline during post intervention period of revascularization therapy in acute ischemic stroke patients will help in achieving a reduction in stroke volume at 3 months. Citicoline is a widely used neuroprotectant and is approved by DGCI for use in India. The current standard of care in acute ischemic stroke within window period is thrombolysis with or without endovascular therapy with stent retrievers. The role of neuroprotective therapies to salvage the ischemic penumbra is not clear. Most of the neuroprotective drug trials have included patients after the critical window period. Those patients undergoing revascularization therapy are expected to have a good ischemic penumbra. Our study is targeting this specific group of patients with intervention of citicoline immediately after the revascularization therapy so that the effect is maximum. Citicoline has never been used concurrently in any clinical trial involving endovascular therapy. The largest clinical trial on citicoline, ICTUS trial also did not have a single patient who underwent endovascular therapy. Moreover, no study has effectively studied the role of Citicoline in acute stroke immediately after or during revascularization (either thrombolysis or endovascular therapy).

The CAISR trial is a single center, prospective, randomized, open-label controlled trial with blinded outcome evaluation. It will be conducted at department of neurology and neuroradiology, All India Institute of Medical Sciences, New Delhi, India. We plan to include all acute stroke patients eligible for revascularization therapy (thrombolysis or endovascular thrombectomy) in the study. Informed consent will be taken for citicoline administration. The patients will be randomized after giving the standard of care treatment for acute stroke. Randomization will be performed using a computer-generated simple randomization sequence. In the citicoline arm, intravenous citicoline 1000mg will be given immediately after the revascularization therapy (thrombolysis/endovascular thrombectomy) and then every 12 hours for 3 days followed by oral citicoline 1000 mg every 12 hours for 6 weeks. The intravenous citicoline will be infused in a 100 ml saline solution bag and infused during 30–60 min. The control arm will receive 100 ml intravenous normal saline which will also be given immediately after the revascularization procedure and then every 12 hours for 3 days followed by oral multivitamin available in AIIMS pharmacy every 12 hours for 6 weeks. The primary outcome of the study is the reduction in stroke volume documented by MRI brain done within one hour of revascularization therapy and at 6 weeks. The secondary outcomes are MRS (0-2), NIHSS (0-2), Barthel Index >=95 at 90 days. Blinded outcome assessment will be done. The study will be conducted according to GCP guidelines and will be registered at clinical trials registry India. All adverse events and SAEs will be reported as per the GCP guidelines.

[figure not shown]

# PART II: TECHNICAL DETAILS OF PROJECT

1. **Research hypothesis**

Administration of citicoline immediately after reperfusion therapy (intravenous thrombolysis or endovascular thrombectomy) will salvage the ischemic penumbra in acute ischemic stroke patients.

# Research question

Whether administration of intravenous followed by oral citicoline in acute stroke patients immediately after reperfusion therapy (thrombolysis or endovascular thrombectomy), will help in achieving a reduction in stroke volume (MRI brain imaging) at 6 weeks and better clinical outcome at 12 weeks?

# Background and Rationale

The current standard of care in acute stroke within window period is intravenous thrombolysis and/or endovascular therapy with stent retrievers. ^1^ In the immediate management of acute stroke, apart from restoring brain perfusion by thrombolysis or endovascular thrombectomy, preservation of ischemic penumbra from further damage is a major research target.^2^The role of neuroprotectants in this scenario had been explored in various animal models and results were promising. But none of these drugs have been effective in phase 3 trials. One of the promising neuroprotectants is citicoline, an exogenous form of cytidine-5ʹ-diphosphocholine (CDP-choline) and an intermediate in phosphatidylcholine pathway.^3-5^ During ischemia, phosphatidylcholine is broken down into free fatty acids, which leads to production of free radicals that causes ischemic injury. In animal studies citicoline has been shown to decrease this cell membrane breakdown, causing increased phosphatidylcholine synthesis and decreased levels of free fatty acids. Moreover, citicoline treatment has been shown reduce infarct volume in animal models.

Citicoline is a widely used neuroprotectant in management of stroke. It is approved by DGCI for use in stroke and traumatic brain injury. Citicoline has been evaluated in various clinical studies.^6-8^ None of these studies showed any treatment efficacy. A meta-analysis of four placebo-controlled, double-blinded RCTs of citicoline in moderate-to-severe ischaemic stroke showed that citicoline improved recovery at 3 month follow-up^3^. This individual patient data pooled meta-analysis showed that moderate to severe stroke patients might benefit if citicoline was started within 24 hours of symptom onset.^4^Later a study- level meta-analysis showed some benefit of citicoline in disability reduction.^9^ The ICTUS trial was designed to confirm the findings of these meta-analysis.^5^ It had 2298 moderate to severe ischemic strokes patients who presented within 24 hours from symptom onset. But it was stopped in 2011 due to futility.

The primary outcome in ICTUS trial was recovery at 90 days assessed by a global test combining the favorable responses from three outcome scales: Barthel index (95–100), mRs (0–1), and NIHSS (0– 1). There was no difference in the 90-day global outcome end point (OR, 1.03; 95% CI, 0.86–1.25; P=0.364).^5^

Very few studies on citicoline have been conducted in India. Ghosh S et al studied the effect of citicoline on 100 patients of stroke (ischemic and hemorrhagic stroke).^10^ They showed that in stroke patients who present within 48 h of onset, management with citicoline improved the outcome (MRS, NIHSS and Barthel Index) at the end of both 1st and 3rd months. This was also observed in all stroke groups. None of the patients in this study received either thrombolysis or endovascular therapy. But this study was methodically weak. They did not provide details of randomization or concealment. Moreover, neither the treating physicians nor the outcome assessors were blinded to the drug allocation. Mitta M et al assessed the efficacy of edavarone and citicoline in 78 acute ischemic stroke (3-24 hours) patients.^11^ They included both anterior and posterior circulation strokes. The study had three arms- edavarone, citicoline and control groups. Edavarone group had better neurological outcome (MRS) at 3 months. They had excluded patients who presented within 3 hrs. None of the patients received any thrombolysis or endovascular therapy. Moreover, there was no blinding in allocation or outcome assessment. Hence it is difficult to make any strong conclusions from these studies. No study has been conducted in India which assessed the role of citicoline in patients undergoing reperfusion therapy.

# Stroke Volume

Citicoline has been shown to reduce the stroke volume in animal studies. In a double-blind placebo- controlled study on acute stroke patients (< 24 hours) conducted by Warach et al using diffusion weighted imaging (DWI), oral citicoline 500 mg/day was used for 6 weeks.^12^ They assessed the progression of stroke volume from baseline to 12 weeks. There was no change in the primary outcome (change in stroke volume) at 12 weeks in 81 patients studied. Even though a big difference in the percentage change of lesion size was found in favor of citicoline, the variance in the placebo group was also large, thereby preventing a statistically significant effect. There was a significant difference in reduction in stroke volume favoring citicoline in the secondary analysis. The authors attributed the negative results to small sample size and they assume that a sample size required to demonstrate an effect with a significance level of 0.05 and a power of 80% would be 58 per arm.

CASIR would be different from this study in the following aspects:

1. Includes all acute ischemic stroke patients undergoing reperfusion therapy, irrespective of the time frame
2. Uses intravenous citicoline followed by oral citicoline (as in ICTUS trial)
3. Citicoline is given immediately after the reperfusion therapy
4. The sample size is larger
5. Includes patients with both anterior and posterior circulation stroke
6. Patients with any deficit will be included

# Rationale

The role of citicoline in patients undergoing reperfusion strategies was never studied exclusively. CAISR is single center, prospective, randomized, open-label, controlled trial with blinded outcome evaluation, aiming to find the role of citicoline in acute stroke patients undergoing reperfusion therapy. The patients undergoing reperfusion therapy are a specific subgroup of stroke patients who may have a large ischemic penumbra and neuroprotectants may have an important role in salvaging those tissues. CAISR is targeting this specific group of patients with intervention of citicoline given immediately after reperfusion therapy so that the effect is maximum.

# Safety profile of Citicoline

The ICTUS trial showed that Citicoline is a safe drug with no significant adverse events.^4^ There was no significant difference in serious adverse events or other adverse events between citicoline and placebo arm. Mortality was comparable between the two groups (221 [19%] of 1148 patients in the citicoline group vs 242 (21%) of 1150 in the placebo group; p=0·31). Citicoline is approved by DGCI for use in stroke and traumatic brain injury.

1. **Preliminary work done if any:** Nil
2. **Objective:**

To find out whether administration of citicoline immediately after reperfusion therapy will cause reduction in stroke volume compared to standard treatment

1. **Detailed methodology including study design and outcome measures**

Study type: Interventional

Study design: Allocation: Randomized

Intervention Model: Parallel Assignment Masking: Blinded outcome assessment

Number of groups: 2 groups (Citicoline arm and Control arm)

Citicoline arm: Intravenous citicoline 1000mg during the revascularization therapy (thrombolysis/endovascular thrombectomy) and then every 12 hrs for 3 days followed by oral citicoline 1000 mg every 12 hrs for 6 weeks. The intravenous citicoline is infused in a 100 ml saline solution bag and infused during 60 min.

Control arm: Intravenous 100 ml normal saline will be given immediately after the revacularisation therapy (thrombolysis/endovascular thrombectomy) and then every 12 hrs for 3 days followed by oral multivitamin available in AIIMS pharmacy every 12 hrs for 6 weeks. The intravenous 100 ml saline solution will be infused in 60 min.

[figure not shown]

**Inclusion Criteria:**

1. Age >= 18 yrs
2. Suspected acute ischemic stroke based on clinical and radiographic evidence as determined and documented by the AIIMS stroke team
3. Participants must meet criteria for intravenous thrombolysis or intra-arterial thrombectomy as determined and documented by Stroke Neurologist and Interventional Neuroradiologist at AIIMS
4. Signed informed consent **Exclusion Criteria:**
5. Intracranial hemorrhage
6. Known allergic reactions to components Citicoline or contrast allergy
7. CT or conventional MRI evidence of brain tumor, subarachnoid and/or intracerebral and/or intraventricular hemorrhage
8. Previous disorders that may confound the interpretation of the neurological scales
9. Pre-existing dementia, when dementia implies a disability, measured as a score of 2 or higher in the previous MRS
10. Patients under current treatment with citicoline

# Outcome

# *Primary Outcome*

The primary outcome will be change in stroke volume from baseline to week 6.

# *Secondary Outcome*

MRS 0-2 at 90 days

NIHSS 0-2 at Day 90

Barthel Index >=95 at D90

# Imaging Protocol for Stroke Volume assessment

MRI brain will be done in any of the following machines: 3T Philips Achieva, 3T Ingenia, 1.5T GE optima. All images will be acquired in axial sequence. The MRI parameters assessed are as follows:

|  | 1.5T GE Optima | 3T Achieva | 3T Ingenia |
| --- | --- | --- | --- |
| DWI | TR: 6000 NOA: 2  TE:77 SBS: 0.5  ST: 5 Matrix: 128*128 | TR: 4050 NOA: 1  TE:96 SBS: 1  ST: 4 Matrix: 163*129 | TR: 3684 NOA: 1  TE:87 SBS: 1  ST: 4 Matrix: 152*122 |
| 3D T1W | TR: 8.47 NOA: 1  TE:3.27 SBS: 0  ST: 1 Matrix: 256*256 | TR: 8.2 NOA: 1  TE:3.74 SBS: 0  ST: 1 Matrix: 240*240 | TR: 8 NOA: 1  TE:3.6 SBS: 0  ST: 1 Matrix: 240*240 |
| 3D FLAIR | TR: 6500 NOA: 1  TE:92 SBS: 0  ST: 1.2 Matrix: 256*224 | TR: 4800 NOA: 2  TE:275 SBS: 0  ST: 1 Matrix: 240*240 | TR: 4800 NOA: 2  TE:300 SBS: 0  ST: 1 Matrix: 240*240 |
| SWI | TR: 74 NOA: 0.7  TE:47.5 SBS: 0.8 ST: 1.6 Matrix: 320*256 | TR: 31 NOA: 1  TE:0 SBS: 0  ST: 0.9 Matrix: 384*384 | TR: 6000 NOA: 2  TE:77 SBS: 0.5  ST: 5 Matrix: 128*128 |
| TOF MRA | TR: 19 NOA: 1  TE:2.8 SBS: 0.6  ST: 1.2 Matrix: 320*192 | TR: 14.84 NOA: 1  TE:3.45 SBS: 0.75 ST: 1.5 Matrix: 380*243 | TR: 23 NOA: 1  TE:3.45 SBS: 0.7 ST: 1.4 Matrix: 400*266 |

NOA: Number of averages SBS: Space between slices ST: Slice thickness

# Data analysis plan

The primary analysis will be an intention to treat analysis. The assumption is that the lesion volume would decrease in 39% of the placebo arm and 65% of the citicoline-treated patients, we estimated that 116 (58 per group) completed patients (baseline and week six MRI assessments completed) were required to detect this difference with 80% power.

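### The 80% power is calculated for a yes/no outcome (any decrease in lesion volume, 39% vs 65%), while the declared primary outcome is change in stroke volume

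*Protocol*

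**What the plan says.** The Primary Outcome section reads: "The primary outcome will be change in stroke volume from baseline to week 6". The summary that opens the protocol, with its second scan also set at week six, words it this way: "The primary outcome of the study is the reduction in stroke volume documented by MRI brain done within one hour of revascularization therapy and at". Both name a quantity measured on two scans. Neither gives a cut-off or a responder rule.

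The Data analysis plan sizes the trial on the assumption that "the lesion volume would decrease in 39% of the placebo arm and 65% of the citicoline-treated patients". The number of patients follows from this: "we estimated that 116 (58 per group) completed patients (baseline and week six MRI assessments completed". The target is stated at the end of the same sentence, where these patients "were required to detect this difference with 80% power". The section names no significance level, test, mean change or SD. The proportion with a decrease does not appear under Secondary Outcome either; that section lists only the MRS, NIHSS and Barthel Index outcomes at day 90.

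The Stroke Volume section describes an earlier diffusion-weighted imaging study of 81 patients. Its primary outcome, change in stroke volume, showed no effect. The protocol's explanation is that "the variance in the placebo group was also large, thereby preventing a statistically significant effect". A secondary analysis of volume reduction favoured citicoline. The same section reports that study's own estimate of the size needed: "a significance level of 0.05 and a power of 80% would be 58 per arm".

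**The concern.** A power statement is a property of one variable and one comparison. Here the variable that was powered (did the lesion shrink, yes or no) is not the variable declared as primary (by how much did the volume change). The two can behave very differently. The first depends only on the sign of each patient's change, the second on its size and spread. The protocol's own account of the earlier study shows that the spread can decide the result.

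What is at stake is the meaning of the primary result. If volume change is analysed and the result is null, the protocol gives no basis for saying that the trial had 80% power to find an effect. If the proportion is analysed, the power statement applies, but to an outcome that the protocol does not list.

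**Working it through.** **Inputs.** Proportions 0.39 and 0.65, 58 per group and 80% power come from the Data analysis plan. Alpha of 0.05 is stated only for the earlier study in the Stroke Volume section; two-sided 0.05 is therefore an assumption. The mean difference and SD of volume change are not given.

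**Step 1: reproduce the plan's figure as a two-proportion comparison.** With pooled p = (0.39 + 0.65)/2 = 0.52 and difference 0.26:

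n per arm = [1.960 × √(2 × 0.52 × 0.48) + 0.842 × √(0.39 × 0.61 + 0.65 × 0.35)]² / 0.26²
= [1.960 × 0.7065 + 0.842 × 0.6822]² / 0.0676 = 1.959² / 0.0676 = 56.8, so 57 per arm.

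Power at 58 per arm = Φ[(0.26 × √58 − 1.960 × 0.7065) / 0.6822] = Φ(0.873) = 80.9%.

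The stated 58 per group is thus reproduced to within one patient per arm. Exact calculation gives 81.2% for the uncorrected test (75.6% for Fisher's test). The magnitude and SD of volume change do not enter this formula at all.

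**Step 2: what 58 per arm means for a difference in means.** The standardised difference detectable with 80% power is (1.960 + 0.842) × √(2/58) = 2.802 × 0.1857 = 0.52 SD. With power = Φ(d × √(58/2) − 1.960):

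| Difference (SD) | Power at 58 per arm | n per arm for 80% |
| --- | --- | --- |
| 0.2 | 19% | 393 |
| 0.3 | 37% | 175 |
| 0.4 | 58% | 99 |
| 0.5 | 77% | 63 |
| 0.6 | 90% | 44 |

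The protocol does not say where in this table it expects to be.

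**Step 3: can 39% and 65% be carried over to volume change?** Only with a distributional assumption. If changes are normal with equal SD and a decrease means a value below zero, the shift is z(0.65) − z(0.39) = 0.385 + 0.279 = 0.66 SD, and power at 58 per arm is about 95% (94% for a t-test).

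Volumes are likely to be skewed, so the same shift was also simulated on log-normal volumes. The assumed ranges are a baseline log SD of 0.8-1.3 and an SD of log change of 0.4-1.0, with means set so that 39% and 65% of patients show a decrease. Power at 58 per arm:

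- t-test on raw change in ml: about 42-74%
- Wilcoxon test on raw change: about 85-90%
- t-test on log change: about 93-95%

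Repeat runs move the ends of these ranges by a point or two. The same patients and the same 39%/65% assumption give power well below or well above 80%, depending on how volume change is analysed.

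**The case against.** The strongest reply is that no loss of power has been shown, and that stands. A reader might infer from the raw-ml figures that the trial is underpowered. The documents do not support this. They name no test, give no SD, and do not commit to raw millilitres; on the same simulated data a rank test or a log-scale analysis does better than the yes/no comparison. The SDs behind all three ranges are assumptions.

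Two further inferences should also be left aside. One is that patients without a measurable lesion at baseline would erode the power of the yes/no comparison: the protocol gives no rate for such patients and does not say whether 39% and 65% already count them. The other is that counting any decrease is too crude an endpoint: that criticises an outcome the protocol has not adopted, and says nothing about the mismatch.

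It can also be said that reduction in stroke volume, as the summary words it, might be meant as a responder outcome, with the Data analysis plan supplying the operational definition. That is possible, and option (a) in the fix allows for it. But the protocol does not say so, whereas every dichotomised secondary outcome is given its cut-off.

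Lastly, a statistical analysis plan that is not shown may name the test. It could settle the analysis, but the protocol's outcome definition and its power statement would still disagree with each other.

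**Conclusion.** The contradiction is real and lies within the protocol. The only power statement is for the proportion with a decrease in lesion volume, which is listed nowhere as an outcome. For that comparison, 58 per arm is adequate: 80.9% power at an assumed two-sided 0.05. For the declared primary outcome the power is unknown. It reaches 80% at about 0.52 SD, and could lie on either side of 80% depending on an unstated difference, SD, scale and test. The conclusion is that the stated 80% is attached to the wrong variable, not that the sample is too small.

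**What to change.** Make the outcome definition and the power statement agree by one of two edits, before any outcome data are compared by arm. Neither changes the 58 completers per arm.

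(a) If the responder rate is meant: state in the summary and under Primary Outcome that the primary outcome is the proportion of patients whose lesion volume is lower at week 6 than at baseline. Define it fully, including how patients with no measurable baseline lesion are classified. Keep the existing calculation and add its alpha and sidedness.

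(b) If volume change as a quantity is meant: restate the Data analysis plan for that variable on a named scale. Log change or a rank test is preferable to raw ml. Say that 58 per arm has 80% power for a difference of about 0.52 SD, and label this as a detectable difference, since working back from a fixed n does not justify an effect size. Stop claiming 80% power from 39% and 65%, and list any decrease in lesion volume as a supportive secondary outcome. If the sponsor's expected difference is below about 0.52 SD, the text should say that power is under 80%.

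The cost is a wording amendment to the summary, Primary Outcome and Data analysis plan (and Secondary Outcome under (b)), with no extra patients or scans.
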